#### Missing data handling

Clinical and laboratory data will be monitored for completeness. Missing data will be addressed *via* multiple imputation using chained equations (MICE), incorporating baseline covariates, clinical outcomes, and molecular features. We have defined a maximum acceptable loss-to-follow-up rate of 10%. If the actual loss rate exceeds 10%, we will compare baseline characteristics of completers and non-completers to assess potential bias. Sensitivity analyses by comparing complete-case and imputed datasets will be reported to demonstrate the impact of missingness on key study findings.

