##### Consideration for machine learning modeling

The novel lung cancer recurrence prediction model will be constructed based on machine-learning algorithms (section 5.2). For the model development, we adopt a ratio of 6:2:2 for the training, validation, and test sets. This division ratio is based on the consideration that 60% training provides adequate data for model fitting and feature selection, while 20% validation allows unbiased hyperparameter tuning, and 20% test ensures a fully held-out assessment to guard against overfitting. This ratio balances model complexity and evaluation rigor, as recommended for medium-sized cohorts.^[21, 22, 23]^ When 173 patients are recruited for statistical power in the training set, a total of 289 cases are required.

In summary, to address the above three dimensions of statistical consideration and the disruption caused by loss to follow-up, we plan to enroll 300 patients in the first phase. This provides sufficient power for survival analysis while also accommodating downstream modeling requirements.

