### Machine learning model development and validation

The patients recruited in the first phase of this study will be randomly divided into training set, test set and validation set according to the ratio of 6: 2: 2. Considering the “events per variable” (EPV) rule, we apply the following steps to develop a robust recurrence prediction model. First, we will not treat all molecular features as separate predictors. Instead, we will compute summary metrics to reduce dimensionality (see section 5.1). Then Least Absolute Shrinkage and Selection Operator (LASSO) regression will be applied within the training subset to identify the most informative predictors, where the penalty parameter will be selected *via* grid search in nested 5-fold cross-validation. This procedure typically yields less than 9 variables, satisfying EPV≥10 given an expected 80 events (26.7% of the 300 patients).

All parameter tuning will be confined to the training set to avoid information leakage. Machine learning-based classifiers will be implemented on the training set with 1000 rounds of ten-fold cross validation. In each round, the training set will be split into 10 subsets (folds); in each fold, a model will be trained on nine of the subsets and then validated on the remaining subset to tune the hyperparameters. Then we will apply all obtained models to the test set and compare the performance measurements. The optimal method will be used to construct the final model. The tested algorithms included: adaptive boosting (AdaBoost), decision tree, logistic regression, linear support vector machine (Linear SVM), radial basis function kernel support vector machine (RBF SVM), naive Bayes, nearest neighbors, neural net, quadratic discriminant analysis (QDA), random forest, and extreme gradient boosting (XGBoost). All machine learning algorithms have a solid research foundation.^[35]^

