We will assess C statistics (area under the receiver-operator characteristic curve [ROC-AUC]), calibration, and clinical utility (decision-curve analysis) in the validation and test set. Finally, we determined an algorithm for developing predictive models, which has been widely popularized in the machine learning community and has excellent scalability, high running speed and state-of-the-art accuracy. It has better average performance than other algorithms in tests. Therefore, it is chosen for further optimization. The model willed be externally and respectively validated on two additional cohorts of NSCLC patients from published database^[10,11]^ and subsequent phases of the CLEVER study to confirm reproducibility and generalizability. If necessary, we will recruit a multi-center prospective multi-region cohort from collaborating institutions of medical alliance for further verification.

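### The only missing-data rule puts clinical outcomes in the imputation model and does not exempt the recurrence prediction model; followed as written, it would leak outcomes into the held-out sets

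*Protocol article*

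**What the plan says.** Under *Missing data handling* the protocol article sets a general rule, "Missing data will be addressed", by MICE "incorporating baseline covariates, clinical outcomes, and molecular features". It names no analysis to which the rule does or does not apply. It adds a check: "Sensitivity analyses by comparing complete-case and imputed datasets will be reported".

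Under *Machine learning model development and validation*, first-phase patients are "randomly divided into training set, test set and validation set according to the ratio of 6: 2: 2". The safeguard in that section reads "All parameter tuning will be confined to the training set to avoid information leakage". Imputation is not mentioned. ROC-AUC, calibration and decision curves are to be assessed in the validation and test sets, and external validation is planned in two published cohorts and later phases of the study.

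Under *Consideration for machine learning modeling*, the reason given for the split is that "20% test ensures a fully held-out assessment to guard against overfitting".

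**The concern.** In an association model, leaving the outcome out of the imputation weakens the covariate–outcome relation, so including it is correct. In a prediction model the outcome of a new patient is unknown. If it helps to fill in that patient's predictors, the score contains some of the answer it is meant to predict.

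The predictors here are summary metrics computed from molecular features, and both molecular features and outcomes are named in the imputation model. Imputation is not parameter tuning, so the stated safeguard does not close this route. If imputation also precedes the ten-fold cross-validation, the held-out folds are affected in the same way. At stake is the discrimination reported for the recurrence model, and unlike sampling error the bias runs in the favourable direction only.

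**Working it through.** **Inputs from the article.** N = 300 and 80 expected events, 80/300 = 26.7%, which reproduces the stated percentage. The 6:2:2 split gives 180 training, 60 validation and 60 test patients. Expected test-set events: 0.2 × 80 = 16, leaving 44 non-events. The article states no AUC and no rate of missing predictor values, so there is no figure of its own to reproduce on this point.

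**Assumptions (not in the article).** Eight independent normal predictors; values missing completely at random at 5, 10, 20 or 30% per predictor; five imputations by chained normal regressions; logistic model with a small ridge penalty; 400 simulated studies per setting. Two scenarios: moderate signal (complete-data test AUC 0.71) and no signal (0.50).

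**Compared.** (C) complete data. (A) One imputation run over all patients with the outcome included, which is the rule taken literally. (B) Training rows imputed with the outcome; test rows imputed without it from training-set fits. For A, the AUC was pooled in two ways: computed in each imputation and averaged (A1), or computed once on the mean score over imputations (A2). B is shown on the mean score.

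| Scenario | Missing | C | A1 | A2 | B | A1 − C | A2 − C |
|---|---|---|---|---|---|---|---|
| Signal | 5% | 0.711 | 0.713 | 0.720 | 0.703 | 0.002 | 0.009 |
| Signal | 10% | 0.711 | 0.713 | 0.726 | 0.693 | 0.002 | 0.015 |
| Signal | 20% | 0.712 | 0.722 | 0.750 | 0.676 | 0.010 | 0.038 |
| Signal | 30% | 0.712 | 0.729 | 0.773 | 0.654 | 0.017 | 0.061 |
| None | 5% | 0.506 | 0.514 | 0.516 | 0.506 | 0.008 | 0.010 |
| None | 10% | 0.501 | 0.517 | 0.519 | 0.501 | 0.016 | 0.018 |
| None | 20% | 0.501 | 0.538 | 0.548 | 0.503 | 0.037 | 0.047 |
| None | 30% | 0.501 | 0.558 | 0.580 | 0.501 | 0.057 | 0.079 |

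Repeating A and C with two other random seeds (600 studies per setting each) gave the same excesses to within 0.005, with standard errors of 0.001 to 0.004.

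**Reading.** With signal, A exceeds C, so losing data appears to improve the model; that can only come from the outcome. With no signal, A departs from 0.50 and B does not.

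**Scale.** Hanley–McNeil standard error for AUC 0.71 with 16 events and 44 non-events: Q₁ = 0.71/1.29 = 0.550; Q₂ = 2 × 0.71²/1.71 = 0.590; variance = [0.71 × 0.29 + 15 × (0.550 − 0.504) + 43 × (0.590 − 0.504)]/(16 × 44) ≈ 0.0065; standard error ≈ 0.08.

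**The case against.** The missing-data text never mentions the prediction model, and the prediction section never mentions imputation. The order of imputation and splitting is unstated, the only stated intent is to avoid leakage, and nesting detail often sits in an analysis plan, which is not shown here. All of this is true, and it makes the point conditional. It does not remove it, because the article does more than stay silent: it fixes one rule with outcomes in it and exempts no analysis.

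A reader might infer that the AUC **is** inflated. The article does not support that: nothing has been reported, and the text does not say that jointly imputed data feed the classifier. A reader might also take the whole gap between A and B (0.773 against 0.654 at 30% missing) as the inflation. Part of that gap is information lost, and noise added, when test predictors are imputed without the outcome. The excess over complete data is the more cautious measure, and it depends on pooling, which the article does not state. Nor was any effect on sensitivity, specificity or decision curves simulated.

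The missingness rates are assumed. Eligibility requires sufficient tissue and blood and excludes patients without clinical-pathologic, imaging or follow-up data, which limits missing values. It does not require complete omics data: paraffin samples are taken only from sufficiently large tumours, while the GeoMx and imaging mass cytometry assays use paraffin tissue. Low missingness therefore cannot be presumed, and high missingness is not shown.

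The complete-case comparison and the external validation could reveal a discrepancy. They do not correct the main estimate, and the imputation rule does not withhold outcomes in external patients either.

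**Conclusion.** The point holds as a conditional one. The outcome-inclusive imputation is right for the DFS and OS models. Applied as written to the prediction model, it conflicts with the held-out test set that the article promises, and the safeguard on tuning does not cover it.

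The resulting optimism in test AUC, over complete data, would be about 0.00–0.02 at 5–10% missing per predictor, which is small beside a standard error of about 0.08. At 20–30% missing it would be about 0.01–0.06 with moderate signal and 0.04–0.08 with none, or up to 0.09 allowing for simulation variation. It is zero if predictors are complete. These sizes rest on assumed missingness, independent predictors, a logistic model and the two pooling choices shown. The direction follows from the mechanism. The correction is worth making before analysis because it is cheap and the bias is one-sided.

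**What to change.** Add to *Missing data handling*, with a cross-reference in the machine-learning section: for the recurrence prediction model, the imputation model is fitted in the training data only and refitted within each cross-validation fold, with the outcome allowed for training rows. It is then applied to validation, test and external patients without any outcome variable. Keep outcome-inclusive MICE for the DFS and OS association analyses. It would also help to state how the AUC is pooled over imputations and to report missingness per predictor.

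Cost: one or two sentences and a modest pipeline change, since imputation must run inside the folds. The reported AUC may be lower, but it would describe what the model can do when the outcome is not yet known.

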#### Confounding bias correction

To control for baseline imbalances between the neoadjuvant and naïve cohorts, we will implement the three methods as follows: (1) Propensity Score Matching (PSM): A logistic regression–derived propensity score will be used for 1: 1 nearest-neighbor matching (caliper = 0.2), including age, sex, smoking status, clinical stage, and ECOG performance status. Balance will be checked *via* standardized mean differences (<0.1). (2) Multivariable Regression: DFS and OS will be modeled in the unmatched full cohort, adjusting for the same covariates to verify robustness. (3) Subgroup Analyses: Pre-specified stratified analyses by clinical stage (I *vs*. II–IIIA) and ECOG (0 *vs*. 1) will be performed. Interaction p values will assess heterogeneity of treatment effect.

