## Introduction

Lung cancer, with non-small cell lung cancer (NSCLC) accounting for 85% of cases, stands as the malignancy with the highest mortality worldwide.^[1]^ An increasing body of cancer research has led to an unprecedented view of the molecular landscape of lung cancer throug next generation sequencing techniques, including DNA sequencing and RNA sequencing.^[2,3]^ Tumor evolution, as a key concept in understanding the onset and progression of cancer, not only contributes to tumor heterogeneity but also results in individual treatment differences. Through multi-region sampling and advanced sequencing technologies, researchers can uncover the evolutionary trajectories of tumors across different temporal and spatial scales. As the largest study of the evolution of NSCLC to date, the TRAcking NSCLC Evolution through therapy [Rx] (TRACERx) study employs multi-region sampling to investigate various aspects of lung cancer, including clonal evolution, genomic instability, and intratumoral heterogeneity to identify prognostic biomarkers that can inform treatment strategies and improve patient outcomes.^[4, 5]^ However, this study primarily involves patients of Western ancestry, which means it provides valuable insights into the biological mechanisms and progression of lung cancer within this specific population.

Lung cancer has significant racial differences, with significant variations in incidence, progression, and outcomes across different ethnic groups.^[6]^ These disparities are influenced by a complex interplay of genetic, environmental, and lifestyle factors. Studies have shown that genetic mutations, such as those in the EGFR and ALK genes, occur at different frequencies in Eastern and Western populations, leading to variations in treatment responses and prognoses.^[7, 8]^ Furthermore, a study comparing 305 cases of lung adenocarcinoma in individuals of East Asian ancestry with 249 cases in individuals of European ancestry found that the East Asian group exhibited more stable genome, characterized by fewer mutations and copy number changes. This finding highlighted important ancestry differences in lung cancer between Eastern and Western populations.^[9]^ However, for the eastern lung cancer multi-region lung cancer study, the explorations were limited due to the small sample size.^[10, 11]^ To sum up, it is necessary and urgent to establish a large multi-region sampling cohort of Chinese lung cancer population.

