#### Inclusion and exclusion criteria

##### Inclusion Criteria

(1) Age ≥ 18 years old; (2) Stage I-IIIA operable NSCLC (ninth AJCC); (3) Sufficient tumor tissue and blood sample with a suspected tumor with a short diameter of at least 15 mm on the preoperative image; (4) NSCLC was confirmed by histopathology, and clinical, imaging and follow-up data were available; (5) Eastern Cooperative Oncology Group (ECOG) Performance Status of 0–1; (6) Written informed consent.

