#### Patient management

In the CLEVER study, all eligible patients are presented at a weekly multidisciplinary tumor board meeting. Decisions regarding neoadjuvant therapy versus upfront surgery are made by consensus based on published authoritative guidelines, taking into account tumor stage (II–IIIA generally considered for neoadjuvant), resectability, and patient preference. Once the treatment plan is determined, research staff obtain written informed consent from participants in the hospital room. The following two questions are explained in detail to ensure that patients fully understand. First, this study involves repeated blood sampling of eight scheduled time points over two years. Potential risks (*e.g*., transient pain, bruising, hematoma, infection) are described, and standard phlebotomy precautions are assured. Second, this study involves a two-year follow-up schedule, including clinical visits and imaging studies. Patients are informed of data confidentiality measures and their right to withdraw at any time without affecting clinical care. Patients treated with direct surgical resection belongs to the Naïve cohort while those undergoing surgical resection following neoadjuvant immunotherapy belongs to the Neoadjuvant cohort). For patients assigned to the neoadjuvant cohort, the consent form includes additional sections that explain the risk and benefit from the neoadjuvant therapies. Participants have the opportunity to ask questions and are provided contact information for study coordinators and the ethics committee. Comprehensive clinical information is collected from all participants, including age, gender, smoking history, radiological image characteristics, and histopathology descriptions.

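### The pre-specified stage I versus II–IIIA treatment interaction rests on few or no treated stage I patients, and the full-cohort model cannot expose confounders that the propensity score also omits

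*Protocol article*

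**What the plan says.** All references are to the Protocol article.

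- **Inclusion Criteria** admit operable NSCLC of stages I to IIIA.
- **Patient management** leaves the choice between neoadjuvant therapy and upfront surgery to tumor-board consensus under published guidelines, "taking into account tumor stage (II–IIIA generally considered for neoadjuvant), resectability, and patient preference". The neoadjuvant cohort is those resected after neoadjuvant immunotherapy.
- **Confounding bias correction** sets out three methods. The first is 1:1 propensity score matching with a caliper of 0.2, the score "including age, sex, smoking status, clinical stage, and ECOG performance status", and a balance check on standardized mean differences. The second is regression: "DFS and OS will be modeled in the unmatched full cohort, adjusting for the same covariates to verify robustness". The third is subgroup analysis: "Pre-specified stratified analyses by clinical stage (I *vs*. II–IIIA) and ECOG (0 *vs*. 1) will be performed". It adds: "Interaction p values will assess heterogeneity of treatment effect".
- **Introduction** says that EGFR and ALK mutation frequencies differ between Eastern and Western populations, "leading to variations in treatment responses and prognoses".

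Histology, driver status, resectability and patient preference are not in the covariate list.

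**The concern.** The subgroup cut falls where the article's own allocation rule says overlap between the cohorts largely ends. A test of whether the treatment effect differs between stage I and stage II–IIIA needs treated stage I patients with events. Without them the model either fails to converge on that term or returns a very wide estimate with a large p value. Such a p value is easily read as a consistent effect across stages when it carries almost no information.

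The regression raises two further points. It would report one hazard ratio for a stage I–IIIA population although nearly all the information on treatment comes from II–IIIA. It is also offered as a robustness check on the matched analysis while adjusting for the same five covariates. A confounder missing from the score is missing from the regression too, so the two can agree and share the same bias. The endpoints affected, DFS and OS, are the study's primary endpoints.

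**Working it through.** The article gives no cohort split, event count or power for neoadjuvant versus naïve, so there is no stated figure to reproduce.

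**1. Precision of the stage interaction**

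Inputs from the article: 300 first-phase patients (Consideration for machine learning modeling), 80 expected events (Machine learning model development and validation) and two-sided 0.05 (Statistical analysis).

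Assumptions, not in the article: 60 to 120 neoadjuvant patients; 70% of the naïve cohort in stage I; an event rate in II–IIIA 2.5 times that in stage I; 80% power.

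Formulas, with e the expected events in each of the four stage-by-treatment cells:

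- SE of the log ratio of HRs = √(1/e₁ + 1/e₂ + 1/e₃ + 1/e₄)
- detectable ratio of HRs = exp{(1.96 + 0.84) × SE}

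Example with 60 neoadjuvant patients, 10% of them stage I:

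- Neoadjuvant: 6 stage I, 54 stage II–IIIA. Naïve: 168 stage I, 72 stage II–IIIA.
- Stage I event rate = 80 / (174 + 2.5 × 126) = 80/489 = 0.164; stage II–IIIA rate = 0.409.
- Expected events: 1.0 and 27.5 in stage I, 22.1 and 29.4 in II–IIIA.
- SE = 1.07; detectable ratio = 19.8.

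Over 60 to 120 neoadjuvant patients:

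| Share of neoadjuvant patients in stage I | Patients in that cell | Expected events | SE | Detectable ratio of HRs | Chance of no event in that cell |
|---|---|---|---|---|---|
| 0% | 0 | 0 | undefined | not estimable | certain |
| 2% | 1.2–2.4 | 0.2–0.3 | 1.74–2.30 | 132–626 | 0.69–0.81 |
| 5% | 3–6 | 0.5–0.9 | 1.13–1.47 | 24–62 | 0.39–0.59 |
| 10% | 6–12 | 1.0–1.8 | 0.83–1.07 | 10–20 | 0.15–0.34 |
| 20% | 12–24 | 2.0–3.7 | 0.63–0.79 | 5.9–9.1 | 0.02–0.11 |

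If the cell has patients but no events, the interaction estimate still diverges. OS cannot do better, because the article counts death as a DFS event and OS events are therefore no more numerous.

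**2. What stage I contributes to the full-cohort hazard ratio**

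Cox simulation, 400 runs per setting, N = 300. Assumptions: half the patients in II–IIIA and half of those treated; hazard in II–IIIA 2.5 times that in stage I; two years of follow-up; true HR 0.70 in II–IIIA; true HR in stage I either 0.70 or 1.5. About 72 events per run. Simulation error on the log HR is about 0.3/√400 = 0.015.

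| Stage I patients treated | Full cohort, stage-adjusted HR | Restricted to II–IIIA |
|---|---|---|
| 0% | 0.68–0.70 | 0.70–0.71 |
| 3% | 0.68–0.71 | 0.69–0.70 |
| 10% | 0.69 (stage I HR 0.70) or 0.80 (stage I HR 1.5) | 0.69 |

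The percentages here are of stage I patients, not of neoadjuvant patients. With 150 stage I patients, 10% treated is 15, and 15/(15 + 75) = 17% of the neoadjuvant cohort. The SD of the log HR is 0.27–0.32 for the full cohort and 0.28–0.31 when restricted, so restriction costs almost no precision.

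**3. The shared covariate list**

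Patient management names stage, resectability and patient preference as decision factors. Of these, only stage enters the score and the regression. For an omitted binary factor, the multiplier on the treatment HR is

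(1 + p₁(HR − 1)) / (1 + p₀(HR − 1)),

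with p₁ and p₀ its prevalence in the neoadjuvant and naïve cohorts. Assume p₀ = 50% and p₁ = 10% to 40%:

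- Factor HR 2.0: from 1.1/1.5 = 0.73 to 1.4/1.5 = 0.93.
- Factor HR 0.5: from 0.95/0.75 = 1.27 to 0.80/0.75 = 1.07.

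All these inputs are assumed, and they treat the raw prevalence gap as remaining after adjustment. They show only that either direction is possible.

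**The case against.** Four objections deserve weight.

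- **A reader might infer that the interaction simply cannot be estimated.** The article does not support that. It says stage II–IIIA is generally considered, which leaves room for some treated stage I patients. Strict non-estimability needs an empty or event-free cell; otherwise the test is merely uninformative. This objection stands and limits the wording.

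- **A reader might infer that keeping stage I in the regression biases the treatment effect.** Stage is adjusted for, and the simulated full-cohort HR stayed at 0.68–0.71 against a true 0.70 with 0–3% of stage I treated. It moved to 0.80 only with 10% treated and an assumed opposite effect in stage I. Matching with stage in the score and a caliper would also tend to leave most stage I naïve patients unmatched. What survives is that the hazard ratio is labelled for a wider population than the one that identifies it.

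- **A reader might infer that omitting EGFR/ALK status confounds the effect by a known amount.** The article does not list driver status or histology among the board's decision factors. Its Introduction sentence concerns differences between populations, not allocation within this cohort. No size or direction follows from the documents. The better-documented omissions are resectability and patient preference.

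- **Driver status from the study's own sequencing is not a clean baseline covariate.** Study tissue is taken at surgery, which in the neoadjuvant cohort is after treatment. The Discussion notes that some such patients reach pathological complete response, which may leave no tumor to sequence. Adjusting for it could introduce response-related missingness in one cohort. This stands and shapes the fix.

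The powered comparison in the article is also high-risk versus low-risk, not neoadjuvant versus naïve, which limits the weight of the point.

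**Conclusion.** The point holds in limited form. Under the article's own allocation rule, the stage I versus II–IIIA interaction will be non-estimable or uninformative. Its detectable ratio of HRs is about 10–20 if 10% of neoadjuvant patients are stage I, still 5.9–9.1 at 20%, and far larger below 10%. These figures use the article's 300 patients and 80 events but depend on the assumed cohort split, stage mix and event-rate ratio.

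The unmatched full-cohort model would attach a stage I–IIIA label to an effect identified essentially from II–IIIA. Agreement between it and the matched analysis would not be evidence against confounding by anything missing from their common covariate list. The documents do not establish that the treatment effect is in fact confounded, or by how much. Residual confounding by histology, driver status or resectability is possible, with size and direction unknown.

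**What to change.** - Restrict both the matched and the regression comparison of neoadjuvant with naïve patients to stage II–IIIA, and report stage I descriptively.
- Drop the stage I versus II–IIIA interaction test, or replace it with II versus IIIA.
- Add histology and resectability, both as assessed before treatment, to the propensity score, the standardized-mean-difference check and the Cox model.
- Add EGFR/ALK status only where it was determined before treatment, and do not take it from sequencing of post-neoadjuvant surgical tissue. Where it is unavailable, state it as possible residual confounding of unknown size and direction.

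The first two changes are analysis wording. The comparison set becomes smaller, but the patients removed carry almost no information on treatment. The covariate change needs pre-treatment histology and the board's resectability assessment in the analysis data. Histopathology is already collected for all participants; the article does not say whether the resectability assessment is recorded.
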